### Study Procedures in Phase 4: Action Evaluation

The theoretical framework that will guide the intervention evaluation is the *Integrated Model of Training Evaluation and Effectiveness* (IMTEE) (36). According to the IMTEE, the needs' analysis' results (i.e., data gathered during Phase 1) inform the content and design of the intervention, which enhances changes in participants and in organizational payoffs. Accordingly, the intervention evaluation will examine *intervention content and design* (i.e., satisfaction and perception of the intervention content, quality and appropriateness); *changes in participants* (i.e., perception of self-efficacy, attitudes toward skills taught during the intervention); *organizational payoffs* (i.e., frequency of use or intention to use skills taught in the intervention).

The questionnaire that will be used to evaluate the intervention will be developed to fit intervention specific content and adapted from past research using the IMTEE framework (37, 38). Once developed, it will be pre-tested in healthcare providers (*n* = 10) to ensure items' understanding. Table 1 presents measures assessment by phase.

#### Data Collection After the First Round of Capacity Building Intervention

Participants will be asked to rate their satisfaction regarding the intervention and to evaluate its content, quality and appropriateness (37). They will also be invited to participate in a focus group shortly after the intervention.

#### Quantitative and Qualitative Analysis (First Round of Intervention)

Descriptive statistics will be used to analyze quantitative data assessed with the questionnaire, whereas qualitative data yielded from focus groups will be analyzed using the same methods described in Phase 1.

The second version of the intervention will be refined based on results with the support and guidance of the advisory committee, which will lead to the creation of the second and final version of the intervention.

#### Data Collection After the Second Round of Intervention

For the testing of the second intervention, quantitative data will be collected at pre-intervention (T0), post-intervention (T1, just after the intervention) and at 6-month post-intervention (T2), whereas a qualitative assessment will be conducted at T1 (see Table 1). A questionnaire will be used to assess the following dimensions:

##### Intervention Content and Design

We will adapt and use the questionnaire from the first round of testing to evaluate reactions of participants regarding the intervention at T1 (36).

##### Changes in Participants

We will use 3–5 items to measure perceived self-efficacy to apply the skills taught during the intervention, 3–5 items to evaluate perceived acquisition of knowledge and 3–5 items to assess attitudes toward the intervention content (37, 38) at T0, T1 and at T2.

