**Intervention Testing: Round 2**			
**Participants' reactions**: perception of intervention's content, quality and appropriateness, overall satisfaction	Adapted IMTEE questionnaire^a^ Qualitative assessment (focus group)	Healthcare staff receiving intervention 2 (*n* ~ 50)	T1^d^ T1
**Changes in participants**: perception of self-efficacy, attitudes toward skills taught during the intervention	Adapted IMTEE questionnaire^b^ Qualitative assessment (focus group)		T0, T1, T2^d^ T1
**Organizational payoffs**: frequency of use or intention to use skills taught in the intervention	Adapted IMTEE questionnaire^c^ Qualitative assessment (focus group)		T0, T1, T2^d^ T1

a *Participants will be asked to rate their satisfaction regarding the intervention and to evaluate its content, quality, and appropriateness using a 5-point Likert scale, ranging from 1 (not satisfied at all/improvement needed) to 5 (completely satisfied/very good)*.

b *Participants will be asked to indicate the extent to which they agree with items using a 5-point Likert-scale ranging from 1 (strongly disagree) to 6 (strongly agree)*.

c *To evaluate intentions to use the newly acquired skills, we will ask participants to indicate the extent to which they agree or disagree with statements using a 6-point Likert scale ranging from 1 (strongly disagree) to 6 (strongly agree). Regarding frequency of use, participants will be asked to indicate how often over the past 6 months they applied specific strategies, using a 5-point Likert scale ranging from 1 (never) to 5 (most of the time)*.

d *T0 = before intervention 2; T1 = just after intervention 2; T2 = 6 months after intervention 2*.

A second improved version of the intervention will then be developed based on the findings yielded in the first round of testing and through discussions with the advisory committee. A second round of the intervention will be organized to test it (involving new participants); for this second round, we expect including between 5 and 15 participants by partner institution (*n* ~ 50). The same methods will be applied to evaluate the improved version of the intervention.

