#### Quantitative and Qualitative Analysis (Second Round of Intervention)

Quantitative data will be screened for missing cases, outliers, and normality of distributions using descriptive statistics. Main analyses will comprise multilevel models (i.e., MLM, mixed effects model) (39). MLM examines the effect of time (after receiving intervention) on dependent variables (changes in participants, organizational payoffs). We will include sources of random variability at the group level accounting for between-group differences and another random effects for the individual accounting for within-person differences in the repeated measures. MLM will be adjusted for demographic variables, role (i.e., nurse, physician, administrative staff) and years of experience. Analyses will be conducted using STATA. The significance level will be set at *p* = 0.05.

Qualitative data yielded from focus groups will mirror the analysis methods used in Phase 1.

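### Perceived acquisition of knowledge is to be rated before training, so its T0-to-T1 change cannot be read as learning, and the attitude scale is worded in two ways of which only one has a valid baseline

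*Protocol article*

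**What the plan says.** The section Changes in Participants lists three scales of 3–5 items each. The first is perceived self-efficacy. The other two are introduced as items to "evaluate perceived acquisition of knowledge and 3–5 items to assess attitudes toward the intervention content (37, 38) at T0, T1 and at T2".

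The timing is given under Data Collection After the Second Round of Intervention: "quantitative data will be collected at pre-intervention (T0), post-intervention (T1, just after the intervention) and at 6-month post-intervention (T2"). The second round uses people who were not in the first: "A second round of the intervention will be organized to test it (involving new participants").

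The second-round analysis section makes this dimension an outcome of the main model: "MLM examines the effect of time (after receiving intervention) on dependent variables (changes in participants, organizational payoffs").

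Two other places describe the same dimension differently. Table 1 lists "perception of self-efficacy, attitudes toward skills taught during the intervention" at T0, T1 and T2. The Phase 4 section gives the dimension as "i.e., perception of self-efficacy, attitudes toward skills taught during the intervention". Neither mentions a knowledge scale. Reactions to the intervention itself are collected at T1 only.

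**The concern.** Acquisition is itself a change. Someone who has not been trained cannot say how much they gained from the training. At T0 they may disagree with every item, report what they have picked up in their career, guess, or leave the items blank. At T1 the same words refer to the session just attended. The two scores differ in meaning as well as in level.

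This matters because each participant is compared only with their own baseline. No comparison group would show the same shift in item meaning without the training, so the time effect on this scale mixes any real gain with the change in what is being asked. A significant result could be published as a knowledge gain when the data cannot show one. A baseline collected in this form cannot be repaired afterwards.

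**Working it through.** The plan gives no effect size, SD or power for this scale, so there is no figure to reproduce. The check is mainly a comparison of the sections, with one illustration of sensitivity.

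**Knowledge scale**

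1. Changes in Participants schedules perceived acquisition at T0, T1 and T2.
2. T0 precedes the intervention and round 2 takes new participants, so nobody has been trained at T0.
3. The main model takes the effect of time on this dimension as an outcome. The T0 score on the knowledge scale therefore enters it, unless the lists in Table 1 and the Phase 4 section, which omit knowledge, are taken to govern. The article does not say which does.
4. No other section offers a knowledge measure that could be answered before training.
5. At T1 and T2 everyone has been trained and the question refers to the same event, so that comparison holds.

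**Attitude scale**

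- Changes in Participants: attitudes to the content of the intervention. A person who has not seen the content cannot properly rate it.
- Table 1 and the Phase 4 section: attitudes to the skills taught. Working staff can rate these before training, and the score can later rise or fall.

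The sections conflict, and only the second wording gives a valid baseline.

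**Illustration for the knowledge scale**

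Inputs from the article:
- n about 50; 5 to 15 from each of 5 institutions gives 25 to 75
- significance level 0.05, taken as two-sided
- lowest answer 1

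Assumptions not in the article:
- mean T0 answer at the floor of 1
- SD of the within-person change 0.8 to 1.2
- normal approximation, clustering ignored

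Smallest significant mean change = 1.96 × SD / √n.

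- n = 50, SD 0.8: 1.96 × 0.8 / 7.071 = 0.22
- n = 50, SD 1.2: 1.96 × 1.2 / 7.071 = 0.33
- most favourable (n = 75, SD 0.8): 0.18
- least favourable (n = 25, SD 1.2): 0.47

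Power at a T1 mean of m = Φ((m − 1)√n / SD − 1.96).

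- m = 1.5, n = 50: 0.84 (SD 1.2) to 0.99 (SD 0.8)
- m = 2, least favourable case (n = 25, SD 1.2): Φ(1 × 5 / 1.2 − 1.96) = Φ(2.21) = 0.986

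A mean of 2 is still on the disagree side, so participants could on average deny having acquired knowledge and the rise would still be significant. Table 1's footnote describes a "5-point Likert-scale ranging from 1 (strongly disagree) to 6 (strongly agree"); 2 lies on the disagree side whether the scale has five points or six.

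The direction depends on the T0 level. With a T1 mean of 2, a T0 mean of 1 gives +1, a T0 mean of 2 gives 0, and a T0 mean of 3 gives −1. The floor is plausible, but the documents do not state it.

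**The case against.** The strongest reply is that no item has been written. The questionnaire "will be developed to fit intervention specific content and adapted from past research using the IMTEE framework" and will be pre-tested in 10 providers. A T0 form could ask about current knowledge, and a condensed article names constructs, not items. The authors also kept reactions to the intervention at T1 only, so they know that some items have no baseline. This stands in part: the defect lies in the stated construct and schedule, not yet in a questionnaire. But the text names acquisition, places it at T0, and says nothing of a different T0 form. The pre-test is described as a check that items are understood, not that they can be answered before training.

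A second reply is that the study claims little. The Introduction names self-efficacy and organizational payoffs as the measures taken before, directly after and at 6 months. The limitations section acknowledges regression to the mean, adds qualitative data, and leaves efficacy to a randomized trial. This limits the consequence, because the other repeated outcomes do not depend on the knowledge scale. It does not make the T0 acquisition score meaningful.

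Two stronger readings are tempting and are not supported:

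- A reader might infer that the change must come out positive. It need not. Someone who answers at the floor before training and learns nothing may answer at the floor afterwards, and T0 answers above the floor allow a zero or negative change.
- A reader might infer that two of the three scales in this dimension are unusable. For attitudes, Table 1 and the Phase 4 section already contain a wording that can be rated at baseline, so the problem there is one of consistency.

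**Conclusion.** The point holds for the knowledge scale. As worded and scheduled, its T0-to-T1 change is not a valid measure of learning, and the single-arm design has nothing to separate a training effect from the change in the item's meaning. This follows from the text and needs no numerical assumption. An upward bias is probable only if untrained staff answer near the floor; on that assumption, rises of 0.18 to 0.47 points would be significant across n = 25 to 75 and change SDs of 0.8 to 1.2. Neither the floor nor the SDs come from the documents.

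For attitudes, the finding is limited to the conflict between sections.

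This should be fixed before the questionnaire is finalised. Self-efficacy, intention to use and frequency of use are not affected by it.

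**What to change.** 1. Word the knowledge items as current perceived knowledge, identical at T0, T1 and T2. Alternatively, keep perceived acquisition, collect it at T1 and T2 only, and leave it out of the T0-based model.
2. In Changes in Participants, describe the attitude scale as Table 1 and the Phase 4 section do, with the skills as its object.
3. Add the knowledge scale to Table 1 and to the Phase 4 list, so that the outcomes of the main model are the same everywhere.
4. Use the planned pre-test in 10 providers to confirm that each T0 item can be answered by someone who has not been trained.

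The cost is item wording or the timing of one scale, in a questionnaire still to be developed. No extra assessment or participant is needed. The construct can stay one of perceived knowledge.

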##### Organizational Payoffs

We will use 6–10 items to assess the intention to use and use frequency of the newly acquired skills use over the past 6 months (37, 38) at T0, T1, and T2.

These dimensions will also be evaluated qualitatively through focus group at T1.

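### Frequency of skill use over the past 6 months is also asked just after training, where its recall window is almost wholly pre-training and a change from baseline cannot show changed behaviour

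*Protocol article*

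**What the plan says.** The Organizational Payoffs section assigns 6–10 items to two constructs, intention to use the skills and frequency of using them, and gives both the same schedule: intention and "use frequency of the newly acquired skills use over the past 6 months" are both placed at T0, T1 and T2.

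Table 1 agrees. Its organizational payoffs row for Round 2 lists T0, T1 and T2. Footnote c repeats the look-back for the frequency items: "participants will be asked to indicate how often over the past 6 months they applied specific strategies". Footnote d fixes the visits: "T0 = before intervention 2; T1 = just after intervention 2; T2 = 6 months after intervention 2". The section on data collection after the second round gives the same timing: "post-intervention (T1, just after the intervention) and at 6-month post-intervention (T2".

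The analysis section for the second round makes this outcome a dependent variable: "MLM examines the effect of time (after receiving intervention) on dependent variables (changes in participants, organizational payoffs". It does not say how time is coded or which contrast is of interest. No section limits the frequency items to T0 and T2 or changes the recall period at T1.

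**The concern.** A look-back item measures the period it looks back on, not the day it is answered. At T1 that period ends just after the training, so nearly all of it comes before any taught skill could have been applied. Whatever the training achieves, true use in the T1 window is close to true use in the T0 window.

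Use frequency is the only Round 2 measure that asks what participants actually did. The others cover reactions, self-efficacy, perceived knowledge, attitudes and intention. One of its two post-training administrations cannot register the effect it is scheduled to detect. Two things are at stake. A T1 rise could be reported as an organizational payoff when no behaviour could have changed. And, depending on how time enters the model, the T1 values could weaken the comparison that is informative.

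**Working it through.** The plan gives no figure to reproduce here. Three checks apply.

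**1. How much of the T1 window follows the start of training?**

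Inputs: recall window of 6 months, taken as 26 weeks (Organizational Payoffs; Table 1, footnote c); T1 just after the training (Table 1, footnote d). The gap g between the start of training and T1 is not stated, so a range is assumed. Share = g / 26.

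| Assumed g | Share of T1 window after start of training |
|---|---|
| 0 | 0% |
| 1 day | (1/7)/26 = 0.5% |
| 1 week | 1/26 = 3.8% |
| 2 weeks | 2/26 = 7.7% |
| 4 weeks | 4/26 = 15.4% |

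The overlap of the T0 and T1 windows follows in the same way. It is about 100% if both are answered on one day, and (182 − 7)/182 = 96% if T0 is one week before T1. At T2 the window runs back six months from six months after training, so it covers the post-training period.

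**2. What does each coding of time estimate?**

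Let true use change by d after training and take the T1 window as wholly pre-training. The expected means at T0, T1, T2 are (0, 0, d).

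- Time as a factor: T2 − T0 = d. Recovered in full.
- Linear score 0, 1, 2 in balanced data: the least-squares weights are (−0.5, 0, 0.5), so the slope is 0.5d per step and d over two steps. The T0-to-T2 change is recovered, but the line also implies a 0.5d rise from T0 to T1 that cannot have occurred.
- Time in months, 0, 0, 6: the fit is exact, with d at T2.
- T1 and T2 pooled as post: (0 + d)/2 − 0 = 0.5d. Halved.

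**3. What happens to power?**

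Only n ≈ 50 comes from the protocol (Table 1). Assumed: complete data, SD 1, correlations 0.8 (T0,T1), 0.5 (T0,T2) and 0.5 (T1,T2), d = 0.4 SD, two-sided 5%, no clustering or covariates.

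- T2 − T0: variance = 1 + 1 − 2(0.5) = 1.00. Noncentrality = 0.40 × √50 / 1.00 = 2.83 (49 df). Power 79%.
- Mean of T1 and T2 minus T0: variance = 1 + (1 + 1 + 2×0.5)/4 − (0.8 + 0.5) = 0.45, SD 0.671. Noncentrality = 0.20 × √50 / 0.671 = 2.11. Power 54%.
- 2-df test of time: the differences from T0 have variances 0.4 and 1.0 and covariance 0.2. Noncentrality = 50 × 0.4² × 0.4 / (0.4×1.0 − 0.2²) = 8.89, on F with 2 and 48 df. Power 74%.

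With the T0,T1 correlation varied over 0.7–0.9 and the other two over 0.3–0.7, power for T2 − T0 runs from 65% to 95% and for the pooled contrast from 41% to 79%. The pooled contrast is lower in all nine combinations.

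**The case against.** **The wording may allow intention alone at T1.** Table 1 defines organizational payoffs as "frequency of use or intention to use skills taught in the intervention", the Introduction and the Phase 4 text also join the two with an "or", and footnote c gives frequency no visit of its own. The questionnaire was also still to be developed and pre-tested. This shows that the text can easily be put right. It does not override the Organizational Payoffs section, which joins the two constructs with "and" and schedules both at all three visits.

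**The useful contrast survives.** This stands. With time as a factor, T2 − T0 gives 0.40 with 79% power whether or not T1 was collected.

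**A reader might infer that T1 dilutes the estimated effect toward zero.** The document does not support that as a general statement. Only pooling T1 with T2 halves the estimate, and no section specifies pooling. The coding of time is a detail that an article may leave to the analysis plan.

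**A reader might infer that any T1 shift is simply recall or demand bias.** That is too absolute. Participants answering at T0 have not yet been taught the skills they are asked about. After training they may understand the items differently and re-rate the same months. Such a shift is not changed behaviour, but it need not be bias of those two kinds. Nor is the true change exactly zero by construction if the training runs over some weeks.

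**This is a first evaluation.** The Challenges and Limitations section acknowledges regression to the mean and leaves efficacy to a later randomized trial. This lowers the stakes. It does not address the recall window.

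**Conclusion.** The point holds for the use-frequency items at T1. Their recall window is almost entirely the pre-training period already covered at T0, so a T0-to-T1 change cannot measure a change in behaviour, while the analysis section counts T1 as an observation after the intervention. Intention to use looks forward and can properly change at T1.

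The statistical cost depends on choices that the article leaves open: none for a T2 − T0 contrast with time as a factor, about 5 points of power for a 2-df joint test (74% against 79%), and a halved estimate with 54% power only under pooling. The power figures rest on the assumed SD, correlations and 0.4 SD gain; the halving under pooling does not. The surer harm is misreading a T1 shift as an organizational payoff. The severity is moderate: one visit of one outcome is affected, and the informative comparison exists as designed.

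**What to change.** - Collect and analyse use frequency at T0 and T2 only, with T2 − T0 as the stated contrast.
- Keep intention to use at T0, T1 and T2, and analyse it as a separate outcome.
- Split the organizational payoffs row of Table 1 into intention (three visits) and frequency (two visits), and amend the Organizational Payoffs section to match.

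The timing of T2 needs no new rule. The schedule already places it six months after the training, so its window is post-training as long as it is not sent early.

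The cost is a few lines of protocol, table and questionnaire wording. The T1 questionnaire becomes shorter, and no informative comparison is lost.

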#### Quantitative and Qualitative Analysis (Second Round of Intervention)

Quantitative data will be screened for missing cases, outliers, and normality of distributions using descriptive statistics. Main analyses will comprise multilevel models (i.e., MLM, mixed effects model) (39). MLM examines the effect of time (after receiving intervention) on dependent variables (changes in participants, organizational payoffs). We will include sources of random variability at the group level accounting for between-group differences and another random effects for the individual accounting for within-person differences in the repeated measures. MLM will be adjusted for demographic variables, role (i.e., nurse, physician, administrative staff) and years of experience. Analyses will be conducted using STATA. The significance level will be set at *p* = 0.05.

Qualitative data yielded from focus groups will mirror the analysis methods used in Phase 1.

#### Phase 5: Learning and Refinement

As previously mentioned, Phase 5 will take place after the first round of intervention testing and evaluation. It will aim to refine the intervention based on results yielded in the evaluation from test 1 with support of the advisory committee, thereby creating the final version of the intervention.

### Ethics and Dissemination

This research project does not involve assessment of personal and clinical data; therefore, it was seemed exempt by the Human Research Ethics Committee of Lausanne University Hospital. It will follow the ethical guidelines outlined in the Declaration of Helsinki and is based on informed consent. All participants will receive an information sheet prior to the interview; they will be informed of the nature of the study, its objectives, the procedures involved, the expected timeline, and the potential risks and benefits it may entail. We will obtain written informed consent of participants who will participate in the intervention (6-months assessment). Regarding the exploration phase, we are conducting semi-structured interviews, mostly from distance because of the COVID-19 pandemic and we obtain informed oral consent (we have audio recording of those). Consistent with the approach described above, participants receive the information sheet prior to the interview. A sign language interpreter participate in this process with D/deaf participants to ensure content understanding. Prior to beginning the interview, the research staff carefully explains all the information included in the information sheet and provides time to the participants to ask questions and make comments. No personal clinical data are being assessed, participants being asked to talk about their experience with healthcare providers and to provide insight into how developing an intervention tailored to healthcare providers to improve their communication skills.

Several steps will be taken to ensure data protection and confidentiality. First, all data collected on participants will be retained at the host institution in locked filing cabinets and on secured protected electronic files. Second, all data collected on participants will be identified through a randomly generated, unique personal identification number (PIN). A master list of PINs will be available only to research staff involved in this project.

We will protect data against disclosure in a few ways. First, published reports will be devoid of all identifying information of participants. Further, access to data will only be granted to the research staff explicitly allowed to access them by the study project leaders. Finally, only deidentified datasets will be made available for co-investigators to run potential additional secondary analyses.

